According to the Physical Activity and Exercise Recommendations for Stroke Survivors, the participants will conduct walking training. Before walking training, walking teaching will be held for 1 week. The training time, frequency and intensity were consistent with those of the Tai Chi group. Each session will include 40 min of walking exercise plus 10 min of warm-up and cool down. All participants in the control group will also receive regular medical treatment and health education as the Tai Chi group.

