### Criteria for discontinuing or modifying allocated interventions {11b}

If the study meets any of the following criteria, the interventions will prematurely end. Patients can leave the study at any time for any reason if they wish to do so and will not face any consequences. Patient participation in this study can be ended by the investigator if the patient is uncooperative and/or does not attend study visits. During the study, patients with low adherence can affect the authenticity of the results. Interventions will be discontinued if there are abundant adverse events (AEs) or serious adverse events (SAEs).

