### Concealment mechanism {16b}

Allocation is not concealed and will be revealed to both the participants and the researcher upon randomization.

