## Assignment of interventions: blinding

### Who will be blinded {17a}

In this study, it will be impossible to blind the participants and Tai Chi coaches. To minimize bias, study personnel, such as researchers who perform relevant tests and outcome evaluators, will not have permission of a central stochastic system. Group A will be used to identify the control group, and group B will be used to identify the Tai Chi group, thus blinding the statisticians and outcome evaluators.

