### Plans to promote participant retention and complete follow-up {18b}

The importance of completion of all trials will be informed. The participants will be able to stop at any time by themselves without giving a reason. At each point in the trial, all patients will be prompted to complete the assessments by telephone or WeChat.

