## Statistical methods

### Statistical methods for primary and secondary outcomes {20a}

Statistical analysis will be performed by statisticians who come from the third term using SPSS 20.0 software for Windows. Categorical variables will be expressed in terms of frequency or percentage, and continuous variables will be expressed in terms of mean and standard deviation. Primary and secondary outcome data collected after 13 weeks and 19 weeks will be compared with baseline data, respectively. For normally distributed variables, a *t* test will be used for statistical comparisons between groups. If it is nonnormal, then a nonparametric test is used. *P* values less than 0.05 will be considered statistically significant. To verify that the results are consistent, the primary outcome (change in VO_2Peak_ between baseline and 19 weeks) will be compared between the two groups using intention-to-treat (ITT) and per-protocol subject analysis (PPS). The Pearson correlation or Spearman correlation measures the correlation between two variables.

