## Oversight and monitoring

### Composition of the coordinating center and trial steering committee {5d}

This is a single-center study performed and coordinated at the Beijing University of Chinese Medicine. Day to day support for the trial will be provided by:
Principle investigator: supervise the trial and medical responsibility of the patients.Study coordinator: trial registration, coordinate study visits.Head coach of Tai Chi: Establish the “Six Forms of Tai Chi” criteria and train the coach of each center.

The study team will meet every 3 weeks. There will not be a trial steering committee or stakeholder or public involvement group.

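### Section {11b}, read literally, lets the investigator end an uncooperative patient's participation in the study and not only the training, so week-13 and week-19 outcomes can be lost avoidably

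*Protocol article*

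**What the plan says.** The Protocol article's section {11b} is headed as being about interventions and opens in the same way: "If the study meets any of the following criteria, the interventions will prematurely end". One of the rules that follows is wider: "Patient participation in this study can be ended by the investigator if the patient is uncooperative and/or does not attend study visits". The sentence after it warns that poorly adherent patients can undermine the credibility of the results, which reads as the motive for the rule.

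Under Statistical methods {20a}, the change in VO2peak from baseline to week 19 "will be compared between the two groups using intention-to-treat (ITT) and per-protocol subject analysis (PPS"; the stated purpose is to see whether the two agree. The retention section {18b} says: "At each point in the trial, all patients will be prompted to complete the assessments by telephone or WeChat". It does not say whether this covers someone whose participation has been ended.

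On who knows the arm, section {16b} says: "Allocation is not concealed and will be revealed to both the participants and the researcher upon randomization". Section {17a} says that "study personnel, such as researchers who perform relevant tests and outcome evaluators, will not have permission of a central stochastic system", and adds coded group labels for statisticians and outcome evaluators. Section {5d} gives the principal investigator the task to "supervise the trial and medical responsibility of the patients".

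**The concern.** Stopping training and stopping follow-up are different decisions. ITT compares patients as randomised, including those who adhere badly, so it needs their week-19 outcomes. PPS already describes the adherent patients. A rule that takes poor adherers out of the study does part of the PPS selection before ITT is run, and agreement between the two then says less.

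The avoidable loss is narrower than the sentence suggests. A patient who does not attend visits already lacks those outcomes. What the rule adds is mainly the uncooperative patient who would still have come.

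If such patients do worse and are removed more often from one arm, the patients left in that arm look better than the arm as randomised. The judgement of who is uncooperative is discretionary and might be made with knowledge of the arm. An analysis plan can choose how to treat missing values, but it cannot recover a test that was never done.

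**Working it through.** **1. The texts side by side.** The heading and lead-in of {11b} concern interventions, but the operative sentence concerns participation in the study. {20a} needs week-19 outcomes from all randomised patients for ITT. {18b} prompts all patients, without saying whether removed patients still count. A site that follows the operative sentence as written would stop follow-up.

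**2. Inputs from the Sample size section {14}.** The plan gives no figure for this rule, so only the scale is taken from it.
- Planned difference: 15.2 − 13.0 = 2.2 ml/kg/min.
- Pooled SD: √((4² + 6²)/2) = 5.10.
- Check of these inputs against the plan's own figure: 2 × [(1.645 + 1.282) × 5.10 / 2.2]² ≈ 92.0, rounded up to 93 per group with one-sided α = 0.05. This is within one of the stated 94. Then 94 × 1.2 = 112.8, or 113 per group as stated. Sidedness and the dropout formula are separate questions.

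**3. Assumptions, none of them in the documents.**
- f is the share of an arm removed as uncooperative who would otherwise have attended: 5% or 10%, about 6 or 11 of 113.
- g is how much worse their mean change is than that of retained patients: 1.1 or 2.2 ml/kg/min.
- Available cases are analysed.
- The SD of change is 5.10 if baseline and follow-up correlate at 0.5. At a correlation of 0.8 it is 5.10 × √(2 × 0.2) = 3.22.

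**4. Formulas.** If retained patients have mean m, the whole arm has mean (1 − f)m + f(m − g) = m − fg, so the retained mean is too high by fg. With T for Tai Chi and C for control:
- Bias = fT·gT − fC·gC.
- SE = SD × √(1/(113(1 − fT)) + 1/(113(1 − fC))).
- Two-sided error when there is no true difference = P(|Z + bias/SE| > 1.96).

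**5. Results with 113 per arm.**

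| Removed, one arm vs other | g | Bias | Error, SD 5.10 | Error, SD 3.22 |
|---|---|---|---|---|
| 5% vs 0 | 1.1 | 0.055 | 5.1% | not computed |
| 10% vs 0 | 1.1 | 0.11 | 5.3% | not computed |
| 5% vs 0 | 2.2 | 0.11 | 5.3% | 5.7% |
| 10% vs 0 | 2.2 | 0.22 | 6.1% | 7.9% |
| 10% vs 5% | 2.2 | 0.11 | 5.3% | 5.7% |
| 10% vs 10% | 2.2 | 0 | 5.0% | 5.0% |

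For example, for 10% vs 0 with g = 2.2 and SD 5.10: bias = 0.10 × 2.2 = 0.22, SE = 0.697, error = 6.1%.

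**6. Allowing for the planned 20% dropout.** The SEs above assume no other loss. With 113 × 0.8 ≈ 90 per arm before removals, the 10% vs 0 error falls from 6.1% to 5.9% (SD 5.10) and from 7.9% to 7.3% (SD 3.22). The 10% vs 5% error at SD 5.10 falls from 5.3% to 5.2%. The biases do not change.

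**The case against.** The strongest reply is that the wording is ambiguous and permissive. The rule sits under a lead-in about interventions, it says participation can be ended and not that it must be, and {18b} prompts all patients without exception. An interventions-only reading is possible. This stands as a limit on the point, but it also argues for rewording, because the operative sentence says otherwise.

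Second, VO2peak needs a maximal effort. A patient uncooperative enough to be removed may not give a valid test, so few removals would cost a usable primary outcome. That makes f small. It does not cover SF-36 or the other measures, which could still be taken.

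Third, follow-up after discontinuation may be set out in the full protocol, which is not shown. That is fair, and the point therefore rests on what {11b} states and not on what the article omits.

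Fourth, both arms follow the same schedule ("The training time, frequency and intensity were consistent with those of the Tai Chi group"), so removals may well be balanced, and balanced removal with equal gaps gives no bias. This stands. The exercises differ and patients know which they have, so imbalance is possible, but nothing shows it.

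A reader might infer that an unblinded investigator will choose whom to remove. The documents do not support that. {16b} reveals the arm to the researcher without saying that this person decides removals. The list of personnel in {17a} is given by example, so the principal investigator's absence from it proves nothing.

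**Conclusion.** The point holds as an avoidable weakness of wording. Read literally, {11b} allows uncooperative patients who would still have attended to be lost to the week-13 and week-19 assessments, and this works against the ITT comparison in {20a}.

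Under one-arm removal of 5% to 10% and a gap of 1.1 to 2.2 ml/kg/min, the bias is 0.055 to 0.22 ml/kg/min, which is 2.5% to 10% of the planned 2.2. The two-sided error is then 5.1% to 6.1% at SD 5.10. The highest figure, 7.9% (7.3% after the planned dropout), needs 10% vs 0 removal, the larger gap and a correlation of 0.8 all at once. Every one of these inputs is assumed.

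A reader might go further and conclude that the primary result is materially threatened or that the ITT analysis is invalid. The documents do not show that: the actual removal rates and gap are unknown, and the expected effect is small. The case for acting is that the loss is unnecessary and cheap to prevent.

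**What to change.** Replace the sentence on ending participation with:

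*Training may be stopped by the investigator if the patient is uncooperative or persistently does not attend training. Stopping training does not end participation: the week-13 and week-19 assessments are still sought for every randomised patient unless consent is withdrawn, and CPET is omitted if medically unsafe.*

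The trigger is missed training and not missed study visits, because the visits are to continue in any case.

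Replace the low-adherence sentence with:

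*Low adherence is recorded and is addressed in the PPS analysis; it is not a reason to remove a patient from follow-up or from ITT.*

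Keep the adverse-event rule as a separate sentence, outside the list of reasons that apply to single patients. The patient's own right to withdraw stays as it is.

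The cost is protocol wording, with the ethics review that the protocol requires for any modification. Attendance is already audited under {23}, so recording non-adherence adds little. The downside is that patients who stop training must still be invited to visits already scheduled, and some will decline.

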### Strategies to improve adherence to interventions {11c}

To improve training compliance, the coach will constantly emphasize the significance and benefits of training for participants. After each training session, participants will complete the self-feeling scale to report their feelings in a timely manner. The coach will regularly conduct out WeChat, telephone return visits, and time training.

### Relevant concomitant care permitted or prohibited during the trial {11d}

Conventional drug treatment (antihyperglycemic, antihypertensive, etc.) will be allowed. Patients’ medication status will be recorded continuously. The control group will not be allowed to take Tai Chi training until the end of the 6-week follow-up.

### Provisions for post-trial care {30}

This study will not include any ancillary or posttrial care. There is no compensation budget item for this study.

### Outcomes {12}

#### Primary outcomes

VO_2Peak_: Peak oxygen uptake (VO_2Peak_) is a highly reproducible objective indicator of cardiopulmonary fitness by the cardiopulmonary exercise test (CPET), which reflects the maximum oxygen uptake achieved by the participant through maximum effort. Studies have shown that VO_2Peak_ is positively correlated with regional cerebral blood flow [25]. Measurement of VO_2Peak_ by CPET is generally recognized as the gold standard of cardiopulmonary capacity [26].SF-36: The SF-36 is a general health status parameter designed for population surveys or health assessments. It contains both physical health content (physical fitness, role-physical, body pain, general health) and mental health content (vitality, social fitness, role emotional, mental health). In this study, the SF-36 scale will be used to assess the effects of Tai Chi on the physical and mental health of stroke patients.

#### Secondary Outcomes

Cardiopulmonary fitness-related indicators: vital capacity (VC), oxygen saturation (SPO_2_), heart rate variability (HRV), cardiac output (CO), ejection fractions (EF), maximal voluntary ventilation (MVV), etc.Safety Assessment: Adverse events (AEs) will be observed during the study period, and the degree of correlation with the study measures will be assessed according to a 5-level standard: ① absolutely related, ② probably related, ③ may be related, ④ may be not related, and ⑤ absolutely unrelated. Regardless of whether adverse events were associated with the study, researchers recorded details on the case report form (CRF), including time, symptoms, adverse reactions and seizure frequency, continuous termination time, laboratory examination indexes, treatment methods, and results.

The researchers will be required to report any serious adverse event (SAE) to the research group within 24 hor no later than the second working day. Researchers will sign and date the report and recorded the source when, how, and to whom serious adverse events were reported.

The formula is as follows: Incidence of adverse events = (①+②+③)/Total actual case.

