### Objectives {7}

Based on previous literature and training experience, our hypothesis is that “Six Forms of Tai Chi” training safely improves the cardiopulmonary fitness of stroke patients in the recovery phase.

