### Adverse event reporting and harms {22}

During the entire study, minor or moderate adverse events will be recorded faithfully in CRF. The coordinating center will conduct a comprehensive analysis and assessment of the occurrence of adverse reactions. Serious adverse events occurring during the study period, regardless of whether they are related to the study-related examination and treatment, will be reported to the central research group within 24 h. Study personnel will complete the registration form of serious adverse events, give symptomatic treatment and actively address the event.

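### The protocol's adverse event incidence leaves out events graded as not related, so it is a suspected-related incidence under the wrong name and cannot exceed the all-cause figure

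*Protocol article*

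**What the plan says.** The Safety Assessment part of Secondary Outcomes sets up a five-level causality scale. The upper three levels are "① absolutely related, ② probably related, ③ may be related"; the lower two are "④ may be not related, and ⑤ absolutely unrelated". Collection does not depend on the grade: "Regardless of whether adverse events were associated with the study, researchers recorded details on the case report form". The summary measure does: "Incidence of adverse events = (①+②+③)/Total actual case".

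Safety is also part of the study hypothesis. Objectives {7} states that the "training safely improves the cardiopulmonary fitness of stroke patients in the recovery phase".

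On who knows the allocation, Concealment mechanism {16b} says it is disclosed to participants and to the researcher at randomisation. Who will be blinded {17a} denies testers and outcome evaluators access to the randomisation system and codes the arms A and B. Adverse event reporting and harms {22} has the coordinating centre assess adverse reactions. No section names the person who assigns the causality grade or says that this person is blinded.

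The SAE reporting time appears twice. Secondary Outcomes gives 24 h or "no later than the second working day". Section {22} says SAEs "will be reported to the central research group within 24 h", with no second limit.

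**The concern.** A figure called the incidence of adverse events will be read as the share of patients who had one, whatever the cause. The formula gives something else, because events judged probably or certainly unrelated never enter the numerator.

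The choice matters for two reasons. First, the only defined safety figure will tend to look lower than the quantity its name promises, in a trial whose hypothesis includes safety. Second, a comparison of arms on this figure mixes two things: how often events occur, and how often someone attributes them to the exercise. An all-cause comparison needs no attribution. A related-only comparison does, and the protocol does not say that the attribution is protected by blinding.

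**Working it through.** **No stated figure to reproduce.** The protocol gives no expected AE rate, safety margin or AE power. The check is of the definition, followed by an illustration on assumed rates.

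**Inputs from the protocol.** The formula and the scale (Secondary Outcomes), and 113 patients per arm (Sample size {14}). All-cause rates and attribution shares below are assumptions.

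**Step 1: the definition.** Fix one counting unit. Let a₁ to a₅ be the numbers at grades ① to ⑤, and N the denominator.

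- Formula in the protocol: R = (a₁ + a₂ + a₃)/N
- All-cause incidence: A = (a₁ + a₂ + a₃ + a₄ + a₅)/N
- Difference: A − R = (a₄ + a₅)/N ≥ 0

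So R ≤ A, with equality only if nothing is graded ④ or ⑤. Equivalently R = A × s, where s is the share graded ① to ③.

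**Step 2: size of the gap, on assumed values.**

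| Assumed all-cause A | R at s = 25% | R at s = 50% | R at s = 75% |
|---|---|---|---|
| 10% | 2.5% | 5% | 7.5% |
| 20% | 5% | 10% | 15% |
| 30% | 7.5% | 15% | 22.5% |
| 40% | 10% | 20% | 30% |

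At A = 30%, about 34 of 113 patients have an AE (0.30 × 113 = 33.9). With s = 50%, about 17 are reported (0.15 × 113 = 16.95).

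**Step 3: effect on a comparison of arms.** The formula compares A×s in one arm with A×s in the other, so unequal shares move the result by themselves.

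- Equal rates, mild split: 30/113 = 26.5% in both arms, shares 40% and 60%. The formula gives 12/113 = 10.6% against 18/113 = 15.9%. An uncorrected two-proportion test gives z of about 1.18 and p of about 0.24.
- Equal rates, wider split: 30% in both arms, shares 30% and 60%. The formula gives 0.30 × 0.30 = 9% against 0.30 × 0.60 = 18%. With 113 per arm, a two-sided 5% test would find a difference about 51% of the time.
- Range: over all-cause rates of 20–40% and splits from 40%/60% to 25%/75%, that chance runs from about 17% to about 97%.
- Unequal rates: 40% against 20%, shares 30% and 60%. The formula gives 0.40 × 0.30 = 12% against 0.20 × 0.60 = 12%, so the excess disappears. The all-cause comparison would have about 91% power.

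**Step 4: the counting unit.** The numerator adds three category totals and the denominator is a number of cases. If the totals are events, the ratio is a mean number of suspected events per patient, not a proportion. If they are patients, someone with events in two categories may be counted twice unless each patient is assigned to one. The text does not settle which is meant.

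**Step 5: the SAE times side by side.** Secondary Outcomes adds an outer limit of the second working day; section {22} has 24 h only. Assuming a Monday-to-Friday week, a Friday event reported on Monday meets the outer limit in the first section but can miss the only limit in the second.

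**The case against.** The best defence is that nothing is lost. Every AE goes on the case report form whatever its grade, and section {22} requires all SAEs to be reported regardless of relatedness. As a rate of suspected reactions the formula is usable. Fuller all-cause tables may sit in an analysis plan that is not shown, and their absence from an article is no fault. That stands: data capture is sound and the defect is confined to one summary measure. It does not rescue that measure, which is a stated definition whose name and content disagree.

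Stronger readings are tempting but not supported:

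- *A reader might infer that staff who know the arm decide relatedness.* Section {16b} makes this possible, but {17a} and {22} leave the grader's identity and blinding open. The documents support only that the grade is not stated to be protected by blinding.
- *A reader might infer that attribution decides the trial's safety comparison.* No between-arm AE test is specified. What can be said is that the only defined AE measure depends on the grade.
- *A reader might infer that repeat events inflate the figure.* That follows only if events are counted. The case-based denominator fits a count of patients just as well. If events are counted, the direction of error against a patient-level incidence is not fixed, so the statement that the formula understates holds only on a common unit.
- *A reader might take the all-cause comparison to be free of bias.* Participants know their arm, so spontaneous reporting may still differ. All-cause counting removes the causality judgement, not that.

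**Conclusion.** The point holds as a definitional error. The measure named AE incidence is a suspected-related incidence and, on the same counting unit, equals or falls below the all-cause incidence. It is the only AE measure in the article, it rests on a grade not stated to be blinded, and its counting unit is unclear.

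That the error can only go one way on a common unit follows from the formula alone. Its size does not: every percentage in the illustration depends on assumed AE rates and attribution shares. The between-arm scenarios show what unequal grading could do; the documents give no evidence that grading will be unequal, and the mild split would not reach significance.

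The conflict over SAE reporting time is a separate inconsistency and adds nothing to the weight of the point about the formula. It should be corrected, and the correction is cheap.

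**What to change.** 1. Define AE incidence as patients with at least one AE of any causality divided by all patients randomised to that arm. Report it per arm with the between-arm difference and 95% CI. A treated-only denominator may be added as supplementary; it should not be the main one, because excluding patients after randomisation in an open trial weakens the comparison.
2. Report SAEs in the same way.
3. Keep the ①+②+③ figure as a supplementary result, renamed suspected-related incidence and counted per patient, so that each patient enters once.
4. State who assigns the causality grade and whether that person knows the allocation.
5. Reconcile the SAE reporting times in Secondary Outcomes and section {22} so that one rule appears in both places.

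The cost is a change of wording and one additional table. All AEs are already recorded regardless of grade, so no new data are needed and the sample size is unaffected.
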